### Sample size

Sample size calculations were conducted using Epi Info Version 5 based on prevalence estimates for primary outcomes derived from a population-based Victorian survey of recent mothers [16]. Table 1 shows power calculations for the study with alpha of 0.5 and beta of 0.20, assuming ratios of:

**Table 1 T1:** Sample size calculations

**Exposure comparison (ratio of unexposed: exposed)**	**Outcome of interest**	**Difference**	**Sample size estimate**	**Total number required***
**Spontaneous vaginal birth:forceps/vacuum extraction (2:1)**	Urinary incontinence Faecal incontinence Sexual problems Perineal pain	11% versus 18% 2.6% versus 8% 24% versus39% 20% versus 53%	930 642 360 168	1200 800 450 210
**Emergency caesarean:forceps/vacuum extraction (1:2)**	Urinary incontinence Faecal incontinence Sexual problems	7% versus 18% 3.9% versus 10.5% 29% versus 39%	371 573 841	950 1500 2200
**Elective caesarean:forceps/vacuum extraction (1:5)**	Urinary incontinence Faecal incontinence Sexual problems	2.4% versus 18% 2.8% versus 10.5% 27% versus 39%	276 763 938	900 2500 3100

* Taking into account the relative frequency of different methods of delivery

• 2:1 (unexposed:exposed) for comparison of spontaneous vaginal births with operative vaginal births;

• 1:2 for comparison of emergency caesarean sections with operative vaginal births; and

• 1:5 for comparison of elective caesarean sections with operative vaginal births.

These ratios were based on routinely collected data for women giving birth in Victoria in 1999. Since the five study hospitals are all public hospitals and nulliparity was an eligibility criterion for the study, the ratios were calculated based on confinements of women admitted as public patients for the birth of their first child.

Using these parameters and allowing for 20% loss to follow-up by 18 months postpartum, we estimated that a sample of 1,900 women would be sufficient to test the hypothesis that primiparous women having an operative vaginal birth have a twofold greater relative risk of developing urinary incontinence, faecal incontinence and sexual problems compared with women having a spontaneous vaginal birth, and to detect a relative risk of 2.0 for urinary incontinence for all exposure comparisons.

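### The claim that 1,900 women can detect a relative risk of 2.0 does not follow from Table 1: it fails for urinary incontinence against elective caesarean and depends on the baseline rate for two other comparisons

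*Protocol article*

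**What the plan says.** Table 1 (protocol article, Sample size) gives assumed rates, sample sizes and cohort totals for three comparisons with operative vaginal birth. The text sets "alpha of 0.5 and beta of 0.20" and unexposed-to-exposed ratios of 2:1 (spontaneous), 1:2 (emergency caesarean) and 1:5 (elective caesarean). The spontaneous-birth rows for urinary and faecal incontinence begin "11% versus 18% 2.6% versus 8" (per cent). The elective-caesarean rows read "2.4% versus 18% 2.8% versus 10.5% 27% versus 39" (per cent).

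The closing sentence applies these parameters with 20% loss by 18 months and makes two claims for 1,900 women:

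- They suffice to test whether operative vaginal birth carries a "twofold greater relative risk of developing urinary incontinence, faecal incontinence and sexual problems compared with women having a spontaneous vaginal birth".
- They suffice "to detect a relative risk of 2.0 for urinary incontinence for all exposure comparisons".

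**The concern.** The size of a two-group comparison depends on the contrast assumed. The elective-caesarean urinary incontinence row needs only 276 women because it assumes 2.4% against 18%, a 7.5-fold difference. That row cannot support a statement about a doubling. The same question arises wherever Table 1 assumes a ratio above 2: faecal incontinence against spontaneous birth, and urinary incontinence against emergency caesarean.

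The article lists a sample large enough to detect clinically important differences by method of birth as a distinguishing strength (Abstract; Strengths and limitations) and as an ethical requirement (Ethical issues). Its Analysis considerations section highlights the debate on elective caesarean and urinary incontinence. A reader who trusts the closing sentence could take a null result for that comparison as evidence against a doubling that the study may well miss.

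**Working it through.** **Inputs from the Sample size section.** Rates and ratios as in Table 1; power 80%; loss 20%; 1,900 enrolled, so 1,900 × 0.8 = 1,520 analysed.

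**Assumptions.** Alpha is taken as two-sided 0.05. The printed 0.5 does not reproduce the table, and the sidedness is not stated. Continuity correction is inferred from the rows below.

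**Step 1: ratios in Table 1.**
- Urinary incontinence: 18/11 = 1.64 (spontaneous), 18/7 = 2.57 (emergency), 18/2.4 = 7.5 (elective).
- Against spontaneous birth: faecal incontinence 8/2.6 = 3.08; sexual problems 39/24 = 1.63.

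**Step 2: reproduce Table 1.** Let p1 and p2 be the unexposed and exposed rates, d their difference, k the exposed-to-unexposed ratio, p̄ = (p1 + k·p2)/(1 + k) and q = 1 − p. The unexposed group size is

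n0 = [1.96·√((1 + 1/k)·p̄·q̄) + 0.842·√(p1q1 + p2q2/k)]² / d²,

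and with continuity correction n = (n0/4)·[1 + √(1 + 2(k + 1)/(n0·k·d))]².

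For elective caesarean, urinary incontinence (0.024, 0.18, k = 5): p̄ = 0.154, n0 = 38.6, n = 45.9, total 6 × 45.9 = 276, as stated.

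| Row | Recomputed | Table 1 |
|---|---|---|
| Urinary, spontaneous | 929 | 930 |
| Urinary, emergency | 370 | 371 |
| Urinary, elective | 276 | 276 |
| Faecal, spontaneous | 643 | 642 |

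The rows behind the claims are therefore computed correctly for the contrasts they state.

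**Step 3: group sizes.** The three ratios combine to 10 : 5 : 2.5 : 1 (spontaneous : operative : emergency : elective), which sums to 18.5. With 1,520/18.5 = 82.2 per unit, the groups are 822, 411, 205 and 82.

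**Step 4: power at RR 2.0.** Power = Φ[(d − 1.96·s0)/s1], where s0 is the pooled and s1 the unpooled standard error. The corrected version subtracts ½(1/n1 + 1/n2) from d.

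A relative risk alone does not fix power; one rate must be held. The article does not say which, so both are shown.

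Example, elective caesarean at 9% vs 18%: s0 = 0.0449, s1 = 0.0368; (0.09 − 0.0880)/0.0368 = 0.05, so power is 52%. The correction subtracts 0.0073, giving 44%.

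| Comparison with operative birth | Exposed rate fixed: power (corrected) | Unexposed rate fixed: power (corrected) |
|---|---|---|
| Urinary, elective caesarean | 9 vs 18%: 52% (44%) | 2.4 vs 4.8%: 11% (5%) |
| Urinary, emergency caesarean | 9 vs 18%: 86% (83%) | 7 vs 14%: 74% (69%) |
| Faecal, spontaneous | 4 vs 8%: 81% (78%) | 2.6 vs 5.2%: 64% (58%) |

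Urinary incontinence against spontaneous birth at 9 vs 18% has about 99% power.

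**Step 5: sensitivity of the elective group size.** Table 1's own fraction for that row is 276/900 = 0.307, against 6/18.5 = 0.324 above. It gives about 78 vs 388 women and power of 50% (42%) or 10% (5%).

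**Step 6: smallest RR detectable at 80% power, 1,520 analysed** (uncorrected to corrected).
- Urinary, elective: 2.8–3.1 with 18% fixed; 4.8–5.2 with 2.4% fixed.
- Urinary, emergency: about 1.9 with 18% fixed; about 2.1 with 7% fixed.
- Faecal, spontaneous: about 2.0 with 8% fixed; 2.3–2.4 with 2.6% fixed.

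**The case against.** The best defence is that the sentence rests on Table 1's parameters and that 1,900 covers them. On those contrasts, the rows it names need at most 1,200/0.8 = 1,500 women. Against spontaneous birth, urinary incontinence and sexual problems are planned at ratios below 2, so a claim at 2.0 is the safer one. All of that stands. It shows that 1,900 is enough for the tabulated differences, not that it is enough for RR 2.0 where the table assumed a larger ratio.

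A reader might infer that the faecal incontinence claim is simply false. The documents do not support that. With Table 1's operative rate of 8% held, power is about 80%. The caesarean blocks print 10.5% for the same operative group, and at 5.25% vs 10.5% power is about 90%. The shortfall appears only when the 2.6% baseline is held, so the claim needs a stated baseline, not removal.

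A reader might also quote one power figure for the faecal and elective-caesarean comparisons together. That would mix anchors: holding the exposed rate gives 81% and 52%; holding the unexposed rate gives 64% and 11%.

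Nor do the ratios 3.08 and 7.5 describe whole blocks of Table 1. Each belongs to one row: the other faecal rows have 2.69 and 3.75, and the other elective rows 3.75 and 1.44.

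Finally, recruitment closed in December 2005, so the sample cannot be changed in response. This limits the remedy to what is reported; it does not make the sentence correct.

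**Conclusion.** The closing power statement is wrong as written. Its phrase covering every exposure comparison fails for urinary incontinence against elective caesarean, where power at RR 2.0 is 44–52% with 18% fixed and 5–11% with 2.4% fixed. For urinary incontinence against emergency caesarean (69–86%) and faecal incontinence against spontaneous birth (58–81%), it holds or falls short according to a baseline that the article does not name. The rest of the sentence is sound.

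These figures assume two-sided alpha 0.05, group sizes from the stated ratios, and 1,520 analysed. The Abstract reports more than 1,500 recruited, not 1,900. If exactly 1,500 were enrolled with 20% loss (an assumption), 1,200 would be analysed, and elective-caesarean power at 9 vs 18% would be about 41% (33% corrected).

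**What to change.** Replace the last sentence of the Sample size section in one of two ways:

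- State the rates and ratios that Table 1 actually powered.
- Preferably, give the minimum detectable RR for each comparison at the analysed number, naming the rate held fixed, as in Step 6.

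Withdraw the RR 2.0 claim for urinary incontinence against elective caesarean. Qualify it by baseline rate for urinary incontinence against emergency caesarean and for faecal incontinence against spontaneous birth. Leave urinary incontinence and sexual problems against spontaneous birth as they are.

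The cost is a reworded sentence, a short recalculated table and less favourable stated figures. No extra women are needed.

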#### Recruitment procedures

The estimated number of women giving birth at the five study hospitals prior to study commencement was 12,700 per annum (based on confinements in 1998/99). At the two tertiary level hospitals (accounting for 8,000 births per annum) approximately 40% of births are to women born overseas of non English speaking background, about half of whom were expected to have insufficient proficiency in English to fulfil the eligibility criteria. A minority of confinements at participating hospitals in 1998/99 (2.1%) were to women receiving care as private patients. Based on these figures and allowing for 10% of women booking after 18 weeks gestation (overlapping to a degree with non-English speaking women), we anticipated it would take approximately 20 months to recruit the cohort assuming a response fraction of around 40%.

The main method of recruitment is via mailed invitation facilitated by the study hospitals. Procedures have been established at each hospital to facilitate: (i) identification of eligible women using hospital data systems; (ii) regular weekly or fortnightly mail-outs to eligible women booking in the preceding week or fortnight; and (iii) weekly or fortnightly follow-up reminder cards for women who have not enrolled two weeks after the original mail-out. The invitation package contains: (i) a brief information leaflet explaining the purpose of the study and inviting women to take part; (ii) a plain language statement with further detail about the study and study consent forms; (iii) the first study questionnaire (Q1); (iv) a sheet for recording contact details, and (v) a reply paid envelope for returning the questionnaire, study consent form and contact details to the research team based at Mother & Child Health Research (MCHR), La Trobe University. The information package includes the names and phone numbers of research team members for queries, and gives the contact number for hospital and/or the La Trobe University Ethics Committee, in case any recipient wished to obtain more information or make a complaint. Recruitment procedures were piloted at each study hospital in late 2002 and early 2003. Different procedures for identifying eligible women and handling the mailing out of the invitation packages and reminders were developed to suit each site.

### Follow-up procedures

Following receipt of the baseline questionnaire (Q1) and signed consent form women are mailed a study postcard which acknowledges receipt of the first questionnaire, thanks them for joining the study, and provides a further copy of contact phone numbers for members of the research team. Participating hospitals are notified of all new enrolments, in order for this information to be flagged in hospital data systems. Information regarding births to study participants or any relevant adverse events (e.g. pregnancy losses, admission of baby to NICU, neonatal deaths) is provided by each study hospital to the project data manager on a regular basis.

All contact with study participants after enrolment is managed by the research team based at MCHR. In phase 1 of the study, follow-up is scheduled to occur at: 30–32 weeks gestation, and at three, six, nine, 12 and 18 months postpartum using a combination of self-administered questionnaires and telephone interviews (see Figure 1). Participant contact details and the names, addresses and phone numbers of alternate contact/s are checked and updated at each telephone interview (30–32 weeks gestation, and at nine months postpartum).

**Figure 1 F1:**
[figure not shown]
Flow chart summarising data collection in phase 1 of the Maternal Health Study.

At each questionnaire follow-up, study participants are mailed a copy of the relevant questionnaire, a covering letter, and a reply paid envelope for returning the questionnaire to the research team. Mailed reminders are sent to women who have not returned a scheduled follow-up questionnaire two weeks after mail-outs at three, six, 12 and 18 months postpartum. Further follow-up of women who have not returned a questionnaire four weeks after the original mailing is undertaken by phone by one of the two project co-ordinators.

Telephone interviews at 30–32 weeks gestation and nine months postpartum are conducted by a small team of trained female interviewers using computer assisted telephone interview techniques (CATI). Interviews are arranged at times to suit participants, with up to eight attempts made to contact women in order to complete an interview.

### Ethical issues

The key ethical issues in this study are:

• a worthwhile question in terms of the size of the population affected, and associated morbidity, quality of life and resource implications

• informed consent to participation in the study, and for information to be obtained from hospital medical records, with the proviso that consent may be withdrawn at any time, and that care provided by hospitals and other agencies will not be influenced by decisions about participation

• an adequate sample size to detect clinically important differences in outcome associated with the method of birth

• acceptability of the study instruments and study procedures to participants

• safe-guarding confidentiality of data.

Study procedures for inviting women to participate were designed to give women detailed information about all aspects of the study. As some of the issues covered in study questions are potentially of a personal or sensitive nature, we wanted to ensure that women were made aware of this before consenting to take part. The first study questionnaire which covers symptoms during early pregnancy and prior to pregnancy was included in the invitation package so that women would be fully acquainted with the types of issues covered by the study before giving their written consent to participate. Study materials emphasised that participants were welcome not to answer particular questions if that was their preference, and the telephone interviewers were trained to reinforce this information prior to commencing each interview.

Study procedures, information materials, self-administered questionnaires and interview schedules were piloted to assess acceptability and relevance, and to ensure that any problems relating to the clarity of instructions and explanations were sorted out prior to commencing each stage of follow-up.

Signed consent was sought separately for information to be obtained from individual hospital medical records regarding pregnancy complications, events during labour and birth, and any postnatal complications, including re-attendances at the study hospital after discharge.

A detailed study protocol was developed outlining procedures for managing recruitment and follow-up (available from the investigators on request), which also became the manual for training research staff working on the study. A separate written study protocol was developed as a guide for research staff conducting telephone interviews. All interviewers are female, and women were informed of this in information materials prior to joining the study.

Procedures for safeguarding the confidentiality of participants include: storage of questionnaires and medical records data abstraction forms in a secure location; separation of names and contact details from data, password protected computer access. All staff working on the study are required to sign a statement confirming that they will adhere to study procedures regarding confidentiality.

Ethics approval for the study has been granted by the La Trobe University Human Research Ethics Committee, and by the Human Research Ethics Committees of the Royal Women's Hospital, Southern Health and Angliss Hospital.

### Data collection

A combination of mailed questionnaires and telephone interviews is being used to maximise disclosure of health problems during pregnancy and follow-up. Study instruments incorporate assessment of the frequency and severity of urinary and bowel symptoms, sexual health issues, perineal and abdominal pain, depression and intimate partner violence using previously validated standardised questions where possible. Questions about urinary symptoms (stress, urge and mixed incontinence) are based on instruments previously validated in Australian, Scandinavian and UK populations [17-20]. Assessment of bowel symptoms (leakage of solid or liquid stool, faecal urgency) is based on questions adapted from validated instruments used in Australian community prevalence studies [21-23]. Items on sexual health include questions previously used in the Australian Study of Health and Relationships [24], the Longitudinal Australian Women's Health Study [25] and a recent UK study of women's sexual health after childbirth [5]. Postnatal pain is being assessed using questions adapted from the McGill Pain Questionnaire [26], and the Brief Pain Inventory [27].

The SF-36 is incorporated in questionnaires in early pregnancy, and at six and 12 months postpartum to provide a general measure of health and well-being to be compared with reporting of specific health problems [28]. Assessment of emotional well-being is being made using the Edinburgh Postnatal Depression Scale (EPDS) and the mental health domain of the SF-36. The EPDS is incorporated in questionnaires in early pregnancy and at three, six, 12, and 18 months postpartum. The EPDS was developed to avoid problems with somatic and social items (eg. change of appetite, sleep disturbance) in other standard measures of depression that cannot be interpreted as morbidity in women with a small baby. It has been found to have good sensitivity and specificity when assessed against psychiatric diagnosis of depression in three studies conducted in the UK, and a small Australian validation study [29,30].

The questionnaire at 12 months postpartum incorporates a validated scale to assess intimate partner abuse (shortened Composite Abuse Scale). The shortened CAS comprises eighteen items of actions by a partner that constitute emotional or physical abuse. For each item, women are asked how frequently a specific behaviour has happened to them during the last twelve months. The scale consists of three dimensions – Emotional Abuse, Physical Abuse and Harassment [31]. During pregnancy and at each follow-up after the birth, two items from the longer version of this scale have been included to identify women who are currently afraid of a partner, or who have ever been afraid of any partner.

Assessment of pre-pregnancy health status is incorporated in the baseline questionnaire (Q1) and telephone interview conducted at 30–32 weeks (CATI 1). Data on socio-demographic characteristics, maternal weight and BMI are being collected in the baseline and follow-up questionnaires.

Information is also being collected on: women's general health and recovery after childbirth; contacts with health services, including primary care and specialist services; physical activity and 'time-out' (when someone else takes care of the baby); practical and emotional support, household composition, partners' involvement in parenting and difficulties in intimate partner relationships; participation in paid work, study and access to paid and unpaid maternity leave.

No urodynamic or other physiological investigations are being undertaken because of the potential negative impact on participation and retention of the cohort, and because the study is focusing on symptom-defined problems.

Pregnancy and birth outcome data will be obtained by medical record review (with women's written consent) according to a detailed written protocol. Women's own accounts of events in pregnancy, labour and birth are being collected in the first two study questionnaires (Q1 & Q2) and telephone interview (CATI 1). Key variables include: method of birth; length of labour; duration of pushing; evidence of obstructed labour; use of epidural, spinal or general anaesthesia; birth position, position of fetus in labour, fetal presentation, degree of perineal and other genital tract trauma, gestation, infant birthweight, and head circumference. Information will also be collected on reproductive history; pregnancy and postnatal complications; and re-attendances at the hospital within six months of the birth. A random 10% sample of medical records will be independently reviewed by two research staff. Final coding will be determined by consensus, with re-checking of the medical record if required. Discrepancies that are not readily able to be resolved in this way will be discussed and resolved at regular team meetings with senior investigators. A record will be kept of all coding discrepancies, and notes taken regarding the rationale for final coding. A further 5% random sample of medical records will be independently re-reviewed to quantify the extent and nature of coding discrepancies.

### Data analysis plan

For aim 1 (incidence, severity and duration of maternal health problems):

▪descriptive frequencies and 95% confidence intervals will be calculated for outcomes of interest at baseline and each follow-up, with stratification to determine the extent of clustering of morbidities and to control for timing of onset of symptoms (prior to pregnancy, during pregnancy, after the birth).

For aim 2 (contribution of pregnancy and birth events to subsequent morbidity):

▪proportions of women reporting outcomes of interest by method of birth (spontaneous vaginal births, forceps assisted vaginal births, vacuum extraction, elective caesarean section, emergency caesarean section) and other obstetric risk factors, including: prolonged first stage labour, fetal position during labour, evidence of obstructed labour in second stage; duration of pushing; fetal presentation at delivery, maternal birth position; use of epidural, spinal or general anaesthesia; degree of perineal trauma; infant birthweight; head circumference; gestation at delivery.

▪multivariable analysis will be undertaken to assess the extent to which method of birth makes an independent contribution to each outcome variable, and to combined morbidity (eg. combined faecal and urinary incontinence). Covariates will include significant labour and birth events, timing of onset of symptoms (pre-pregnancy/during pregnancy/post birth), maternal age and maternal height and early pregnancy BMI. A series of stratified and logistic regression analyses will be performed to validate model choices against stratified data. Generalised linear mixed modelling to take account of repeated measures will be used to determine the effect over time on the associations between health outcomes and covariates.

For aim 3 (reasons for non-disclosure of morbidity to health professionals): descriptive frequencies for prevalent cases will be reported for formal and informal help-seeking and treatment, and for non-disclosure at baseline and each follow-up. Analysis will take into account socio-economic background, the severity and duration of maternal health problems, general health status (SF-36) and extent of co-morbidity.

Assessment of the representativeness of the sample in terms of obstetric and social characteristics will be conducted by comparing study participants with routinely collected Victorian Perinatal Data for births at participating hospitals, and all Victorian births, corresponding with the recruitment period. This will provide an estimate of the representativeness of the sample in terms of exposures of main interest (e.g. method of birth), and covariates (e.g. mothers' age, marital status, country of birth, infant birthweight).

